## Abstract

**Introduction:**

Exercise interventions have a strong evidence base for falls prevention. However, exercise can be challenging to implement and often has limited reach and poor adherence. Digital technology provides opportunities for both increased access to the intervention and support over time. Further knowledge needs to be gained regarding the effectiveness of completely self-managed digital exercise interventions. The main objective of this study is to compare the effectiveness of a self-managed digital exercise programme, Safe Step, in combination with monthly educational videos with educational videos alone, on falls over 1 year in older community-dwelling adults.

**Methods and analysis:**

A two-arm parallel randomised controlled trial will be conducted with at least 1400 community-living older adults (70+ years) who experience impaired balance. Participants will be recruited throughout Sweden with enrolment through the project website. They will be randomly allocated to either the Safe Step exercise programme with additional monthly educational videos about healthy ageing and fall prevention, or the monthly education videos alone. Participants receiving the exercise intervention will be asked to exercise at home for at least 30 min, 3 times/week with support of the Safe Step application. The primary outcome will be rate of falls (fall per person year). Participants will keep a fall calendar and report falls at the end of each month through a digital questionnaire. Further assessments of secondary outcomes will be made through self-reported questionnaires and a self-test of 30 s chair stand test at baseline and 3, 6, 9 and 12 months after study start. Data will be analysed according to the intention-to-treat principle.

**Ethics and dissemination:**

Ethical approval was obtained by The Regional Ethical Review Board in Umeå (Dnr 2018/433-31). Findings will be disseminated through the project web-site, peer-reviewed journals, national and international conferences and through senior citizen organisations’ newsletters.

**Trial registration number:**

NCT03963570.

Strengths and limitations of this studyThe method of using a completely self-managed digital exercise programme for delivering fall prevention exercise is novel and will contribute to the evidence of using smartphones and tablets for delivering fall prevention exercise.The Safe Step-exercise programme includes behaviour change support to facilitate maintenance of the new exercise routine.The use of wide inclusion criteria could enhance external validity.A limitation of the study is that large attrition rates are expected due to the study design of no face-to-face interaction, and there is a risk of unequal distribution between groups.To assess intervention reach, the sociodemographic parameters of participants will be compared with the target population.

## Background

About one-third of community-living older adults fall every year,^1 2^ with an increasing frequency with a higher age and frailty level.^3^ In Sweden, falls represent 87% of injury-related hospital admissions in older adults,^4^ with a 30% risk of another fall which requires medical attention in the next 5 years.^5^ Globally, the related healthcare costs are substantial,^6^ and are likely to exponentially increase with the growing proportion of older people.^7^

There is strong evidence that falls among community-living older adults can be prevented both short and long terms using exercise as a single intervention.^8 9^ The most effective types of exercise are balance and functional exercises combined with resistance exercises.^9^ Even though there is a large body of evidence that supports the effectiveness of exercise interventions, up to 52% of older adults engaging in individually targeted fall prevention exercise do not adhere to the exercise over 12 months.^10^

To aid older adults in changing their exercise behaviour, there is a need for tailored exercise interventions that are not only adapted to the individual’s physical function but also promote personal benefits, such as increased or prolonged independence.^11 12^ Furthermore, interventions need to increase motivation for exercise by taking into consideration the older adults’ individual lifestyle, perceived risks of exercise, as well as physical capabilities.^13^ To support self-efficacy for exercise, older adults can be engaged in creating and tailoring their own routines, which has been suggested as a route to improved adherence.^11^ Additionally, support of older adults’ active roles are preferable to having complete dependence on professionals,^7^ and can also improve well-being among older adults.^14^

Home-based exercise provides a practical choice for participants and could solve issues with both accessibility and costs as well as support the older person to self-manage their exercise. According to a large survey, home-based exercises were preferred over other fall prevention strategies, especially in individuals of an older age, those who have recently fallen, or those who are socially disadvantaged.^15^ To exercise at home with occasional visits from instructors has been shown to be effective in preventing falls^16^ as well as to integrate the exercise into everyday activities at home,^17^ which many older adults also prefer.^18^

The use of technology and digital health is emerging as ways of delivering self-managed exercise and fall prevention interventions for older adults.^19–21^ Such digital interventions enable the participants to exercise at preferred times and locations.^22 23^ Technology can further enable the use of tools for behaviour change such as self-monitoring, direct feedback and action planning, which can support self-efficacy for self-management.^24^ Digital technology can, therefore, provide support over time, which is important due to high attrition rates from fall prevention exercise programmes.^10^

There is limited evidence of the effectiveness of smartphones and tablets for delivering fall prevention exercise.^19^ Of those evaluated, the interventions has been combined with the interaction of health professionals.^20 21^ If proven effective, completely self-managed digital interventions with no interaction with a health professional would provide a more rapid and extensive implementation of fall prevention programmes, vastly increasing reach to a wider population. Additionally, it may be economically beneficial due to reduced use of resources from healthcare professionals. In this emerging field, more research is needed regarding the effectiveness of digital interventions with no interaction between healthcare professionals and participants.

We have previously developed a completely self-managed exercise application for smartphones and tablets with a focus on improving physical function and preventing falls, the Safe Step application.^25^ The application provides a large repository of evidence-based exercises in short video formats with associated safety advice. Behaviour change is supported through strengthening of self-efficacy and behaviour change techniques incorporated in the application. The participants are supported to create their individual programme, plan their weekly exercise and monitor their exercise routine in the application. To further support behaviour change, the participants receive motivational feedback and reminders of their planned exercise from a virtual physiotherapist. The exercise programme is influenced by the Otago home exercise programme that has been proven effective in reducing falls among community-living older adults,^26 27^ but also expanded with both easier and more challenging exercises mainly inspired by the Falls Management Exercise programme.^28^ The Safe Step application (v1) was explored in a feasibility study, a participant preference trial comparing the programme to a paper booklet with exercises. Results from a qualitative study showed that the participant using the digital exercise programme found it both easy to use and easy to tailor to their own circumstances.^22^ The majority of the participants exercised at least during 75% of the intervention weeks and one-third of the participants completed more than 75% of recommended exercise time.^29^

To investigate the effectiveness of a self-managed digital exercise programme, this randomised (1:1) controlled trial (RCT) aims to compare the Safe Step application in combination with monthly educational videos with a control group that only receives the educational videos.

The primary aim is to evaluate the effect on fall rate in older community-dwelling adults during a 12-month intervention period. Secondary aims are to evaluate number of fallers, self-reported balance and strength, fear of falling, quality of life, cost-effectiveness, and attrition and exercise adherence. In addition, we will describe sociodemographic parameters of those who are recruited in comparison to the target population in order to assess intervention reach.

## Method

### Participant and public involvement

The Safe Step application has been designed and cocreated with, and for older adults.^25^ In further cocreation sessions, behaviour change components were developed together with older adults to enhance long-term adherence. The feasibility and acceptability of outcome measures have been informed by a feasibility trial. The Prevention of Falls Network Europe (ProFaNE) consensus of a common data set for fall injury prevention trials^30^ and a feasibility study have informed the choice of outcome measures in this RCT. In addition, a small reference group has tested the final questionnaires and provided feedback. A spokesperson for senior citizen organisations in Sweden was consulted regarding recruitment for the RCT study.

### Study design

The 1-year Safe Step RCT study uses a two-arm parallel design with digital interventions. The intervention group receives the Safe Step application, delivered on smartphones or tablets. Both groups will receive an email every month with short educational videos about healthy ageing and falls prevention.

This protocol is reported in line with the Standard Protocol Items: Recommendations for Interventional Trials guidelines.^31 32^ The RCT will be reported according to the Consolidated Standards of Reporting Trials (CONSORT) statement,^33^ and CONSORT EHEALTH criteria.^34^ The health economic evaluation will be reported according to the Consolidated Health Economic Evaluation Reporting Standards statement.^35^

### Participants

At least 1400 and up to 2000 older adults living in the community will be recruited throughout Sweden. The inclusion and exclusion criteria are shown in table 1.

**Table 1 T1:** Inclusion and exclusion criteria

Inclusion criteria	Exclusion criteria
Older adults 70 years or older Fallen or experienced a decline in perceived postural balance during the last year Have access to a smartphone or tablet and uses it regularly Have an own email address and uses it Able to understand verbal and written instructions in Swedish Can rise from a standard height chair without a person helping Can walk independently without a walking aid indoors	Progressive disease where there is likely to be a decline in strength or balance over the next year Perceived memory dysfunction that affect everyday life activities Taking part in more than 3 hours each week of strenuous physical exercise which makes them out of breath (eg, dance, gymnastics, gym exercises, running or skiing)

### Recruitment

To reach the target sample size, at least 1 year is estimated for enrolment of participants starting in September 2019. The recruitment strategies will be directed towards the largest senior citizen organisations with the potential to reach approximately 800 000 members, and information will be distributed via the physiotherapist union, section for older adult’s health. Recruitment strategies will include both digital and non-digital strategies. The digital recruitment strategies include advertisements on webpages and Facebook; posts on open and closed Facebook-pages; emails or digital newsletters directly to members of the senior citizen organisations. Non-digital strategies include advertisements in newspapers and in Swedish magazines commonly read by older adults. Participants will be directed to the open-access project website (www.sakrasteg.se) where the necessary study information is provided to decide on participation. A self-assessment of eligibility will be performed by the participant based on the inclusion and exclusion criteria provided (table 1). On the project website, participants are informed that by providing their email address they will give their informed consent for participation and consent for publication of their pseudonymised data. An email will be sent to them to confirm their registration and verify their email address, including one reminder. When confirmation has been received, a link will be sent to the first baseline questionnaire (figure 1).

**Figure 1 F1:**
[figure not shown]
Flow chart of study design.

### Randomisation and blinding

After completed baseline questionnaire, the participants will be randomised in a 1:1 ratio using permuted block randomisation with randomly varied block sizes. A statistician not involved in the study will generate the allocation list using the randomizeR R-package before enrolment.^36^ A computer programme developed in FLOW, Microsoft Office 365-software, will randomise participants according to the allocation list.

After randomisation, the FLOW programme will automatically send emails with follow-up questionnaires as well as the monthly fall reports and educational videos. In order to include participants, monitor data collection and answer emails regarding technical issues, two members of the research group will be able to see the participant’s email addresses and group allocation in the FLOW system and database. However, no personal contact will occur between researchers and participants regarding the results of their outcome assessments.

Analyses of the outcomes regarding falls and physical function will be made by a researcher blinded to group allocation. Participants will not be blinded due to the nature of the intervention.

### Interventions

After group allocation, the participants will receive an email introducing them to the interventions as described next. Throughout the study, there will be a project email account for questions, and frequently asked questions may gradually be added on the website.

#### Safe Step: digital exercise programme

The Safe Step application was developed by our research group in collaboration with older adults^25 37^ and the software (v2) was programmed by Information and Communications Technology Services and System Development (ITS), Umeå University. Participants allocated to the exercise intervention will receive instructions by email on how to download the application from App Store or Google Play, as well as their personal log-in details.

On the first time use of the application, the participants view an instruction video on how to use the application to create and progress their own individual exercise programme. The participants compose their individual exercise programme choosing 10 exercises from predetermined groups of exercises with a main focus to improve balance (3 groups), increase lower limb strength (4 groups) and improve gait/step (3 groups). The exercises are presented in video format and in increasing levels of difficulty, or with alternatives within each group of exercises. The participants are instructed to choose exercises that are challenging but not too hard. Hence, during balance exercises a feeling of being unstable but not to the extent of losing their balance and falling, and for strength exercises progress when able to easily perform the recommended repetitions. A new exercise should be selected whenever they feel that the current exercise becomes too easy or too difficult. Participants are requested to exercise for 30 min at least 3 days/week, but are also informed that a longer duration of exercising per week will give a better fall preventive effect. After each session, participants will register their activities in the application: completed exercises, exercise duration, experienced well-being of the day of exercise and experience of levels of intensity for balance and strength exercises.

In the application, the participant can make a schedule for their weekly exercise, register activity and monitor their exercise routines (figure 2). They will also be able to set reminders tailored to their personal preferences. Direct feedback and motivational messages will be received from a virtual physiotherapist when exercise is registered. At the beginning of every month of the 1-year intervention period, the participants will receive an email with a new educational video about healthy ageing and fall prevention. The third video contains information on physical activity and exercise, but no suggestions of particular exercises are given.

**Figure 2 F2:**
[figure not shown]
Features of the Safe Step application.

#### Control group

Participants allocated to the control group will receive the same educational videos as those sent to the intervention group. After the 12-month follow-up assessment, the control group will be offered the Safe Step application.

### Data collection

At baseline and 3, 6, 9 and 12 months, respectively, from the participant’s inclusion in the study, an email containing a link to an online questionnaire will be sent to the participants. All collected data will be self-reports, including a 30 s chair stand self-test (30CST). In the absence of completed questionnaires, a reminding email will be sent out after 1 week. If further absence, another email will be sent after an additional week. This reminder will also include a question if they want to withdraw from the study. Data registered in the exercise diary of the application are collected continuously. In the same monthly email as the educational videos, all participants will receive a request to report any falls during the past month by answering a short web-based questionnaire. In the absence of a completed questionnaire, one reminder will be sent after 1 week. All data retrieved from questionnaires, as well as application data, will be coded and reported on a group level.

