### Outcomes

#### Primary outcome

The primary and secondary outcomes, and time points of distribution are presented in table 2. The primary outcome measure will be the rate of falls (fall per person/year) during the 12 months of the intervention. To register falls, a link to a self-report online questionnaire will be sent monthly by email. To be able to report correctly the coming month, participants are asked to make notes of falls in a calendar, preferably the day the fall has occurred. They will be provided with a printable calendar in the email sent out after allocation, but they can also use their own. If a fall is reported, additional questions will be asked about the cause of the fall, potential injuries sustained, need for medical attention and hospitalisation. The number of persons falling during 12 months will be analysed based on the same data as a secondary outcome.

**Table 2 T2:** List of primary and secondary outcome measures

Outcome measures	BA	C	M	3 months	6 months	9 months	12 months
Fall rate† (fall per person/year)			X				
Number of fallers‡ (n)			X				
Number of falls during exercise with Safe Step§ (n)			X				
Fall-related injuries§ (yes/no, need of medical attention, type of injury)			X				
Hospitalisation due to falls§ (yes/no and number of days)			X				
Reach§ (self-reported sociodemographic parameters such as age, sex, years of education, use of smartphone and tablet, number of cohabitants and self-reported health and diagnosis)	X						
Self-administered 30 s chair stand test¶	X			X	X	X	X
The Borg Scale of Perceived Exertion during 30 s chair stand test** (numeric scale, score 6–20)	X			X	X	X	X
Self-rated balance**, ‘How do you perceive your balance?’ (5-level ordinal scale)	X			X	X	X	X
Self-rated leg strength**, ‘How do you perceive your leg muscle strength?’ (5-level ordinal scale)	X			X	X	X	X
Fear of falling¶ (Falls Efficacy Scale-International)	X			X	X	X	X
Health-related quality of life¶ (EQ-5D-5L)	X			X	X	X	X
Experienced positive effects of the exercise intervention§ (nominal scale, optional text field)	X*			X*	X*	X*	X*
Experienced negative effects of the exercise intervention§ (nominal scale, optional text field)	X*			X*	X*	X*	X*
Exercise adherence throughout the intervention reported through an integrated exercise diary in the Safe Step application§,¶		X*					
Exercise adherence, self-reported min/week§				X*	X*	X*	X*
Use and perceived usefulness of educational videos** (4-level ordinal scale)				X	X	X	X

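### As described, the monthly fall report covers only the past month and no step fills an intermittently missed month, so falls in such months are lost, possibly informatively

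*Protocol article*

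**What the plan says.** All references are to the protocol article.

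- **Outcome.** Primary outcome section: "The primary outcome measure will be the rate of falls (fall per person/year) during the 12 months of the intervention".
- **Instrument.** Data collection: "all participants will receive a request to report any falls during the past month by answering a short web-based questionnaire". For this report, "In the absence of a completed questionnaire, one reminder will be sent after 1 week". The quarterly questionnaires get one reminder more: "If further absence, another email will be sent after an additional week".
- **Calendar.** Primary outcome section: "participants are asked to make notes of falls in a calendar, preferably the day the fall has occurred". On its supply: "They will be provided with a printable calendar in the email sent out after allocation, but they can also use their own". Its stated purpose is to help the participant complete the coming monthly report. Returning or transcribing it later is not described.
- **Detail on each fall.** Primary outcome section: "If a fall is reported, additional questions will be asked about the cause of the fall, potential injuries sustained", followed by medical attention and hospitalisation.
- **Schedule.** Table 2 places fall rate, number of fallers, falls during app exercise, fall-related injuries and hospitalisation in the monthly column only. None has an entry at 3, 6, 9 or 12 months.
- **Missing data.** Planned statistical analyses: all available data are analysed by allocation. Multiple imputation is used for data considered missing at random when no more than 40% is missing, and unimputed results are given as a supplement.

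**The concern.** Missing a single report (travel, illness, a hospital stay) is different from leaving the study. The participant comes back, may hold a written note of what happened, and opens another study form within weeks. As described, that form asks only about the latest month, so both the falls and the person-time of the missed month drop out of the primary analysis.

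If reports were missed for reasons unrelated to falling, falls and person-time would go together and only precision would suffer. An injurious fall is, however, itself a plausible reason for not answering that month. Missingness then depends on the unobserved count, and the missing-at-random condition attached to the imputation fails. The same reports are the stated source for number of fallers, injuries and hospital days. Under Economic evaluation they also feed the cost estimates, so the costliest falls could be the ones most often lost.

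Whether the rate ratio is affected depends on the arms differing. The article's own limitations box expects large attrition with a risk that it is unequal between groups. Only the exercise arm receives app reminders and motivational messages, so reporting habits could differ in either direction.

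**Working it through.** **1. What happens to one missed month.** Suppose the April report is missed and the May report is answered. The May form asks about the past month, so April is not covered. Table 2 has no fall item at 3, 6, 9 or 12 months, so the quarterly forms do not cover April either. The calendar may hold April's falls, but no described step asks for them. The reminder after one week is the only described route to April's data.

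**2. The plan's own figure, to set the scale for precision.** Inputs from Sample size: control rate 1 fall per person-year, rate ratio 0.80, overdispersion 1.2, 80% power. The two-sided 5% level is from Planned statistical analyses. Taking 1.2 as a variance-to-mean factor:

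n per group = 1.2 × (1.960 + 0.842)² × (1/1.0 + 1/0.8) / (ln 0.8)² = 425.6

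This is within 2% of the stated 420, so the same reading is used below.

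**3. Loss unrelated to falling (assumed shares).** With a fraction f of person-months reported, SE = √[1.2 × (1/1.0 + 1/0.8) / (n f)] and power = Φ(0.2231/SE − 1.960).

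| Person-months missed | Power, 420 per group | Power, 700 per group |
|---|---|---|
| 0% | 79.5% | 94.9% |
| 5% | 77.4% | 93.8% |
| 10% | 75.2% | 92.6% |
| 20% | 70.2% | 89.5% |

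The 700 column (half of 1400) assumes that everyone otherwise gives a full year, which the plan does not expect. The target of 1400 equals 840/0.60, against 840/0.50 = 1680 if drop-outs gave nothing. It therefore already relies on partial reports.

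**4. Loss tied to falling (assumed shares).** At 1 fall per person-year, about 1 − exp(−1/12) = 8.0% of person-months contain a fall under a Poisson count. At 0.8 the share is 1 − exp(−0.8/12) = 6.4%. Losing fall-months therefore removes falls almost one for one and barely changes person-time. Let c be the proportion of falls captured relative to person-time captured. Then observed ratio = 0.80 × c(exercise)/c(control).

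- 20% lost in the exercise arm, 10% in control: 0.80 × 0.80/0.90 = 0.71.
- 10% lost in the exercise arm, 20% in control: 0.80 × 0.90/0.80 = 0.90.
- 10% lost in both: 0.80 × 0.90/0.90 = 0.80. Of the 420 + 336 = 756 falls expected in 420 per group over a year, about 76 go unrecorded.

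If the lost months are also taken out of person-time, the second case becomes 0.90 × (1 − 0.080 × 0.20)/(1 − 0.064 × 0.10) = 0.89. The first stays at 0.71.

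**5. What a catch-up item could recover (assumed half).** Losses of 20% and 10% become 10% and 5%. The ratio is then 0.80 × 0.90/0.95 = 0.76 or 0.80 × 0.95/0.90 = 0.84, so the bias shrinks but does not vanish.

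**The case against.** A one-month recall window is a defensible choice: short recall is more accurate, and lengthening it for some months is a real trade-off. The article is condensed and does not reproduce the questionnaire, which may be better than its description. Own calendars are allowed and same-day notes are only preferred, so a complete record of a missed month is not assured. Much of the missing time will come from permanent drop-out, given the anticipated 50% attrition, and no catch-up question reaches those people. All of this stands. It limits the gain but does not remove the gap, because the collection schedule and reminder rules are stated and contain no recovery step.

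Four stronger readings are tempting and are not supported:

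- **That a missed month can never be recovered.** There is a reminder, no link expiry is stated, and nothing says that a late reply is refused. The text is silent on recovery and does not exclude it.
- **That late replies shift the window, so that falls are counted twice or not at all.** Link closing dates and exact item wording are operational details that an article commonly leaves out. Nothing shows that participants would count back from the reply date.
- **That the last month is uncovered.** The video email, which carries the fall request, is timed thus: "At the beginning of every month of the 1-year intervention period, the participants will receive an email with a new educational video". The abstract, however, places reporting at the end of each month, and a closing report may well exist.
- **That 0.71 or 0.90 is the expected bias.** These values need a loss specific to fall-months that differs by ten percentage points between arms, and the documents give no such figure.

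**Conclusion.** The point holds as a cheap improvement to how the primary outcome is collected. It is neither a contradiction nor a numerical error. As described, falls and person-time in intermittently missed months are lost, and the planned imputation does not cover months missed because of a fall. Available-case analysis does not cure this either.

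The size is unknown, because no monthly non-response rate is given. If 10% to 20% of person-months were missed at random, power at 420 per group would fall by about 4 to 9 points. Bias in the rate ratio needs two further assumptions: that falling raises the chance of a missed report, and that it does so differently by arm. On the assumed 10% against 20%, a true 0.80 would read as about 0.71 or 0.90. With equal excess loss the ratio is essentially unbiased, but absolute fall rates, injury counts and fall-related costs are understated.

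**What to change.** - When a participant opens the next monthly, quarterly or 12-month form, also ask about any unreported earlier months. For example, ask about falls since the last completed report, with that date filled in from the database, and invite the participant to consult the calendar.
- Ask for the date of each fall, if the form does not already do so, and count each dated fall once.
- Put the same injury, medical-attention and hospitalisation questions to recovered falls.
- Flag recovered months, include their falls and person-time in the primary analysis, and repeat that analysis without them as a sensitivity analysis.
- Report, by arm, how many months were missed and how many were recovered.

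The cost is questionnaire wording, a pre-filled date in the existing survey system and one additional analysis. The downside is longer recall for recovered months, which the calendar limits and the sensitivity analysis checks. Permanent drop-outs remain unaddressed. If the full protocol or the questionnaire already contains such a step, stating it is enough.
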